# Neurological and psychological mechanisms of the specific and nonspecific effects of acupuncture on knee osteoarthritis: study protocol for a randomized, controlled, crossover trial

**DOI:** 10.1186/s13063-020-04908-9

**Published:** 2020-11-30

**Keywords:** Acupuncture, Functional magnetic resonance imaging, Nonspecific effect, Psychological factors, Specific effect

## Abstract

**Background:**

Acupuncture, as one of the promising non-pharmacological interventions, has been proved to be beneficial for patients. However, the magnitude of acupuncture’s specific and nonspecific effects, as well as their neurological and psychological determinants, remains unclear. Therefore, this study is designed to examine the acupuncture efficacy, investigate whether the brain mechanisms between the specific and nonspecific effects of acupuncture are different, and to evaluate how psychological factors affect the acupuncture effects.

**Methods:**

This is a randomized, controlled, crossover clinical trial. A total of 60 patients with knee osteoarthritis will receive 4 weeks of acupuncture treatment and 4 weeks of sham acupuncture treatment in a random order separated by a washout period of 2 weeks. The changes in clinical characteristics based on pain-related scales will be assessed to investigate the clinical efficacy of acupuncture. Resting state functional magnetic resonance imaging (fMRI) scans will be used to identify the brain activity changes related to the specific and nonspecific effects of acupuncture. The questionnaires of psychological factors will be used to evaluate patients’ psychological properties. Correlation and mediation analyses will be conducted among psychological factors, brain activity changes, and symptoms improvement to explore the neurological and psychological correlates of the acupuncture effects.

**Discussion:**

This study will concentrate on distinguishing and clarifying the specific and nonspecific effects of acupuncture. The results of this study may contribute to rationally optimize the acupuncture therapies by flexible application of the specific and nonspecific effects of acupuncture.

**Trial registration:**

Chinese Clinical Trial Registry ChiCTR1900025807. Registered on 9 September 2019

**Supplementary information:**

The online version contains supplementary material available at 10.1186/s13063-020-04908-9.

## Background

The total effects of an intervention (e.g., acupuncture) comprise specific and nonspecific effects [1, 2]. The specific effect is generated by characteristic and inherent components, while the nonspecific effect is generated by incidental elements [3, 4]. Acupuncture, as one of the promising non-pharmacological interventions, has been proved to be beneficial for patients in the application of evidence-based approaches [5, 6]. But the specific effect of acupuncture has been criticized. Several recent randomized trials have found that acupuncture can benefit patients while its total effect is slightly or even no better than sham acupuncture [7–9]. Some researchers attribute the effect of acupuncture to a powerful placebo effect or a nonspecific effect [10]. In addition, the greater effect has been generally observed when compared acupuncture with no treatment rather than with sham acupuncture, also suggesting that nonspecific effect can contribute to acupuncture’ benefits [11]. Therefore, the recognition of specific and nonspecific effects may be important for the selection, conduction, and optimization of acupuncture to improve clinical efficacy [12]. However, the magnitude of acupuncture’s specific and nonspecific effects, as well as their determinants, remains unclear.

Many studies have shown that the size of placebo or nonspecific effect can be influenced by psychological factors, such as expectation, emotion, awareness, and personality [13–15]. And it is worth noting that positive expectation and good doctor-patient communication are both important psychological factors on acupuncture treatment and can enhance efficacy of acupuncture [16, 17]. For instance, Kong found that expectancy could modulate the pain experience on knee osteoarthritis (KOA) patients in both acupuncture and sham acupuncture [18]. Moreover, cumulative evidence suggests that acupuncture may be accompanied by strong psychobiological responses [4]. Therefore, in our study, an emphasis will be placed on exploring the influence of psychological factors on specific and nonspecific effects of acupuncture.

Functional magnetic resonance imaging (fMRI) can reveal the functional changes of the brain and improve our understanding about the central neurological mechanisms of acupuncture [19]. In recent years, fMRI has been applied to investigate the central regulation mechanisms of the acupuncture’s effects [20–22]. Acupuncture and sham acupuncture have relatively different brain responses in the medial frontal cortex, periaqueductal gray, and rostral ventromedial medulla during analgesia [21, 23]. Most clinical trials focus on evaluating abnormal brain activity triggered by the specific effect (acupuncture – sham acupuncture), while ignoring the modulation of nonspecific effect (sham acupuncture) on brain. Interestingly, an fMRI study has found that different pre-treatment functional connectivity characteristics can predict symptom changes for acupuncture and sham acupuncture treatment, respectively [24]. Therefore, fMRI is an appropriate method to distinguish different treatment effects of acupuncture. However, there is lack of evidence on differentiating the neurological mechanisms triggered by specific and nonspecific effects of acupuncture.

It should be mentioned that pain is one of the most important conditions for acupuncture recommended by the World Health Organization, and it is a subjective sensory condition that is sensitive to a placebo response. Knee osteoarthritis (KOA), which is a common disease with chronic pain as the main symptom, is a suitable model for investigating the specific and nonspecific effects of acupuncture. Therefore, we have designed a randomized, controlled, crossover trial to clarify the specific and nonspecific effects of acupuncture. In this study, the first objective is to evaluate the magnitude of acupuncture’s specific and nonspecific effects on treating KOA. The second objective is to assess the central neurological mechanism of acupuncture’s specific and nonspecific effects. The third objective is to explore how psychological factors affect the efficacy of acupuncture.

## Methods

### Study design

This is a randomized, controlled, crossover clinical trial (Fig. 1). In order to accurately clarify the specific and nonspecific effects of acupuncture, a controlled, crossover trial has been designed to control the interference of individual difference (e.g., demographic characteristics, brain metrics and psychological factors) on the results. This trial has been approved by the ethical committees of Dongzhimen Hospital Affiliated to Beijing University of Chinese Medicine (NO: DZMEC-KY-2017-53-02) and registered in Chinese Clinical Trial Registry (NO: ChiCTR1900025807). The protocol will be reported following Standard Protocol Items: Recommendations for Interventional Trials (SPIRIT) statement (Additional file 1). A total of 60 patients diagnosed with KOA according to American College of Rheumatology clinical criteria will be recruited [25]. After inform consent acquisition, all patients will be randomly assigned to group A and group B based on the ratio of 1:1. The patients in group A will receive acupuncture 3 sessions per week for 4 weeks. After a 2-week washout period, the patients in group A will receive sham acupuncture 3 sessions per week for 4 weeks. The patients in group B will receive the reverse intervention process.

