#### Exclusion criteria

The exclusion criteria include the following: (1) history of knee surgery or waiting for knee surgery (e.g., knee replacement or arthroscopy); (2) history of knee injection in the past 6 months or arthroscopy in the past 12 months; (3) knee pain caused by other diseases (e.g., trauma, fracture, gouty arthritis, infection, malignant tumor); (4) psychiatric or neurological disorders (e.g., traumatic brain injury, stroke, Parkinson’s disease); (5) coagulation disorders, severe acute or chronic organic disease; (6) MRI contraindications (e.g., claustrophobia, cardiac pacemaker or other metallic agents embedded within body); (7) severe skull anatomical asymmetry or definite lesions found on magnetic resonance scanning; (8) alcohol or drug abuse; (9) pregnant or lactating or planning a pregnancy; and (10) recent acupuncture in 1 month.

During the trial period, patients with KOA who meet the following criteria will be excluded from the study: (1) protocol violation such as taking analgesic without permission or receiving additional treatment that may interfere with the efficacy of acupuncture, (2) withdrawal of consent for study participation because the patients do not wish to continue, (3) missing more than 6 of 24 acupuncture treatment sessions, and (4) occurrence of a serious adverse event that the doctors consider should lead to termination of trial participation.

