### Clinical outcomes evaluation

The pain-related scales will be used to evaluate the magnitude of acupuncture’s specific and nonspecific effects in treating KOA. The primary outcome will be the change of pain on the Numerical Rating Scale (NRS) after 4 weeks of intervention. And the minimal clinically important improvement (MCII) will be defined as at least 2-point reduction on the NRS, and patients who attain the MCII will be defined as responders [9, 33]. The secondary clinical outcomes will include the change of short-form of the McGill Pain Questionnaire (SF-MPQ) and Western Ontario and McMaster Universities Osteoarthritis Index (WOMAC). The SF-MPQ, which includes sensation and affection of pain [34], will be used to assess the pain quality. The WOMAC consists of three subscales with five-point Likert scale: pain, stiffness, and physical function [35]. Adverse events and blinding assessment during the study will be recorded (Fig. 3).

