### Statistical analysis

#### Clinical data analysis

The continuous variables will be described as the mean (standard deviation) or the median. The categorical variables will be described as the percentage. The comparisons between the two groups will be analyzed by independent sample *t* test, Wilcoxon rank-sum, or *χ*^2^ test in demographic, psychological factors and other indicators. The comparison between the acupuncture and sham acupuncture will be analyzed using general liner model. Intention-to-treat analysis (ITT) will be mainly used to evaluate the efficacy of acupuncture. ITT analysis will be performed to analyze all randomized data, and last observation carried forward (LOCF) will be adopted to impute the missing values. Per protocol analysis will be used and per protocol population will include patients who complete at least 10-session acupuncture during each phase and finish 4 fMRI scans. The specific effect of acupuncture will be calculated by subtracting the effect in sham acupuncture from the acupuncture. The nonspecific effect of acupuncture will be calculated by subtracting the pre-acupuncture from the post-acupuncture in sham acupuncture phase. The data will be statistically analyzed by SPSS software.

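### The 2-week washout is shorter than the 1-month acupuncture-free entry rule, without explanation, and fading acupuncture benefit in phase II would understate the nonspecific effect

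*Protocol article*

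**What the plan says.** The trial is a two-period crossover in which patients receive "4 weeks of acupuncture treatment and 4 weeks of sham acupuncture treatment in a random order separated by a washout period of 2 weeks" (Abstract, Methods). For group A, the Study design section states: "After a 2-week washout period, the patients in group A will receive sham acupuncture 3 sessions per week for 4 weeks". For the other sequence: "The patients in group B will receive the reverse intervention process".

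At entry, item 10 of the Exclusion criteria rules out "recent acupuncture in 1 month". The protocol gives no reason for either interval and does not relate one to the other.

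Under Clinical outcomes evaluation, "The primary outcome will be the change of pain on the Numerical Rating Scale (NRS) after 4 weeks of intervention". Under Clinical data analysis, "The nonspecific effect of acupuncture will be calculated by subtracting the pre-acupuncture from the post-acupuncture in sham acupuncture phase", and the specific effect is the acupuncture effect minus the sham effect. Neuroimaging data evaluation places a baseline scan and an end scan in each phase, and the per-protocol definition counts four scans. Phase II therefore has its own pre-treatment imaging baseline, and the within-phase definition of the effect implies the same for the NRS.

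**The concern.** A group A patient starts sham 2 weeks after a course of 12 acupuncture sessions. If the entry rule were applied again on that day, the patient would not meet it. The protocol does not say why a shorter interval is enough between phases.

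The effect definitions turn this into an estimation problem. A change score within phase II is measured from the post-washout value. If part of the acupuncture benefit is still present then and wears off over the next 4 weeks, the loss is counted against sham. The sham change in group A comes out too small, and so does the pooled nonspecific effect. Within a group A patient the same loss raises the specific effect and lowers the nonspecific effect, so the two can appear opposed for no biological reason. That would carry into the correlation and mediation analyses.

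The magnitude of these two effects is the trial's first objective (end of the Background). The definitions are fixed in the protocol, so an analysis plan that is not shown would inherit them.

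**Working it through.** **Plan's own figures.** The protocol gives two intervals, 2 weeks and 1 month. It gives no figure for carryover, so there is none to reproduce. T, S and the residual fractions below are assumptions.

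**Notation.** T and S are the true improvements (positive = less pain) on acupuncture and on sham. f is the fraction of phase-I benefit present when phase II starts, g the fraction present when it ends, and k = f - g the fraction lost during phase II. Subscripts mark which treatment came first.

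**Expected changes under the protocol's definitions, 1:1 allocation**

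- Group A: acupuncture change T; sham change S - k_T·T.
- Group B: sham change S; acupuncture change T - k_S·S.
- Pooled nonspecific effect = S - k_T·T/2.
- Pooled specific effect = (T - S) + (k_T·T - k_S·S)/2.

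If both treatments lose the same fraction k, the specific effect is (T - S)(1 + k/2).

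**Limit on k under exponential decay.** Phase II starts at day 14 after phase-I treatment and ends at day 14 + 28 = 42. Since 42 = 3 × 14, g = f³ and k = f - f³. This is largest at f = 1/√3 = 0.577, where k = 0.577 - 0.192 = 0.385.

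**Results with assumed T = 3, S = 2 (true specific 1.00, true nonspecific 2.00), same decay for both**

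| Assumed half-life | f | g | k | Nonspecific | Specific |
|---|---|---|---|---|---|
| 7 days | 0.250 | 0.016 | 0.234 | 1.65 (-18%) | 1.12 (+12%) |
| 14 days | 0.500 | 0.125 | 0.375 | 1.44 (-28%) | 1.19 (+19%) |
| 28 days | 0.707 | 0.354 | 0.354 | 1.47 (-27%) | 1.18 (+18%) |
| Worst case | 0.577 | 0.192 | 0.385 | 1.42 (-29%) | 1.19 (+19%) |

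Worst case in full: nonspecific = 2 - 0.385 × 3/2 = 1.42; specific = 1 × (1 + 0.385/2) = 1.19.

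**Sensitivity to T and S.** The relative nonspecific bias is kT/(2S), so it grows with T/S. With T = 2, S = 1 the three half-lives give -23%, -38% and -35%. The relative specific bias stays at k/2.

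**Cases where the result changes (T = 3, S = 2)**

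- Constant residual (k = 0): neither effect is biased.
- Equal absolute loss of 0.5 points after each treatment: specific = 1.00, unbiased; nonspecific = 2 - 0.5/2 = 1.75.
- Loss of 25% of T (0.75) and 50% of S (1.00): specific = 1 + (0.75 - 1.00)/2 = 0.875, understated; nonspecific = 2 - 0.75/2 = 1.63.

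**The case against.** The two intervals do different jobs. One governs eligibility and the other separates trial phases, and both can be followed. A reader might infer a contradiction, or that the protocol itself regards anything under a month as contaminated. The text does not support that, because the entry rule comes without a rationale. What stands is an unexplained inconsistency.

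A reader might also infer that carryover must inflate the specific effect. It need not: the sign depends on which treatment loses more in absolute terms. With equal fractions the bias is proportional to T - S, so it vanishes if acupuncture is no better than sham, a possibility the Background raises itself.

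Larger figures are tempting. With T = 3, S = 2, half the benefit left at the start of phase II and none at its end, one gets +25% and -38%. That requires the residual to vanish completely within phase II, and those T and S cannot give such values under exponential decay.

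It would also be too strong to say that no planned analysis could detect the problem. The general linear model is named without its terms, Fig. 4 is not shown, and period or sequence handling is commonly left to an analysis plan. The point does not depend on that omission. A period term would absorb a loss common to both sequences, but not the part by which they differ.

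Finally, "the minimal clinically important improvement (MCII) will be defined as at least 2-point reduction on the NRS", so a patient who starts phase II below 2 cannot be a responder. This is true arithmetically, but the documents do not show how often it would happen, and responder status is not the primary outcome.

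**Conclusion.** The concern holds as a conditional risk, mainly to the nonspecific effect. The washout is shorter than the acupuncture-free interval at entry and no reason is given. If acupuncture benefit fades during phase II, the pooled nonspecific effect is understated by kT/2. The specific effect is biased only through unequal absolute losses: overstated by (T - S)k/2 if the fractions lost are equal, unbiased if the absolute losses are equal, and understated if sham loses more.

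The sizes of about -29% and +19% rest on assumed T = 3, S = 2 and a shared exponential decay. The documents cannot establish whether any residual exists. Severity is moderate: the trial is described as a pilot and the bias is conditional, but it falls on a quantity the trial sets out to measure and is cheap to guard against.

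**What to change.** Reconcile the Study design and Exclusion criteria sections, or state why the intervals differ. Whether to alter the schedule is for the sponsor, and no interval is proposed here.

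Without touching the schedule or the primary outcome, and documented before unblinding because the trial is already recruiting:

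- **(a)** Prespecify a first-phase-only comparison of group A with group B, adjusted for baseline NRS, as a sensitivity analysis for the specific effect.
- **(b)** Report the nonspecific effect from group B in phase I, which cannot contain carryover, separately from group A's phase-II sham change. If they differ, base the stated magnitude on group B. Write down in advance what counts as a difference, and note that a period effect could also produce one.
- **(c)** Report pre-treatment NRS in phase II minus phase I, by sequence, to show whether pain had returned to its initial level.

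End-of-phase NRS may be added as a supportive contrast. It should not replace the primary change score, since that would alter the estimand.

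**Cost.** All three use NRS values that the change-score definitions already require. The first-phase estimates use about half the data, roughly 24 against 24 completers (30 × 0.80), and lose the within-patient comparison that motivates the crossover. They are therefore less precise, which is why (a) is a sensitivity analysis.

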**Fig. 1 Fig1:**
[figure not shown]
Study flow diagram

### Study setting and recruitment

The study will be carried out at the Dongzhimen Hospital Affiliated to Beijing University of Chinese Medicine. Sixty patients with KOA will be recruited via hospital outpatient clinics, advertisements in hospital social media (WeChat), and flyer displays at community service centers. The recruitment information will provide telephone number so that potential patients can be able to contact the researchers. Two researchers ([name] and [name]) will be responsible for assessing eligibility and providing the study information, such as the objective, intervention, duration, benefits, and risks of the study. Patients who agree to participate in this study will sign an informed consent.

#### Inclusion criteria

The inclusion criteria include the following: (1) age 45–65 years (male or female), (2) duration of chronic knee pain ≥ 6 months, (3) radiologic confirmation of knee osteoarthritis (Kellgren-Lawrence grade II or III) [26] within 12 months, (4) Numerical Rating Scale (NRS) ≥ 4 with in the past week, (5) right-handed; and (6) written informed consent.

#### Exclusion criteria

The exclusion criteria include the following: (1) history of knee surgery or waiting for knee surgery (e.g., knee replacement or arthroscopy); (2) history of knee injection in the past 6 months or arthroscopy in the past 12 months; (3) knee pain caused by other diseases (e.g., trauma, fracture, gouty arthritis, infection, malignant tumor); (4) psychiatric or neurological disorders (e.g., traumatic brain injury, stroke, Parkinson’s disease); (5) coagulation disorders, severe acute or chronic organic disease; (6) MRI contraindications (e.g., claustrophobia, cardiac pacemaker or other metallic agents embedded within body); (7) severe skull anatomical asymmetry or definite lesions found on magnetic resonance scanning; (8) alcohol or drug abuse; (9) pregnant or lactating or planning a pregnancy; and (10) recent acupuncture in 1 month.

During the trial period, patients with KOA who meet the following criteria will be excluded from the study: (1) protocol violation such as taking analgesic without permission or receiving additional treatment that may interfere with the efficacy of acupuncture, (2) withdrawal of consent for study participation because the patients do not wish to continue, (3) missing more than 6 of 24 acupuncture treatment sessions, and (4) occurrence of a serious adverse event that the doctors consider should lead to termination of trial participation.

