### Sample size

Since this is a pilot study, a formal sample size calculation is not performed [27]. According to fMRI studies, a sample size of 20 subjects are sufficient to detect a significant difference with a type I error of 5%, and about 25 subjects are required when *α* = 0.000002, to achieve a stable statistical power [28–30]. Considering a 20% attrition rate and possible excessive head motions occur in the fMRI scanning, we plan to recruit 30 subjects in each group.

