### Interventions

Each type of acupuncture treatment will include 12 sessions of 30-min duration over 4 weeks (3 sessions per week). The date of each patient’s treatment will be recorded, and the number of treatments received by each patient at intervention phase I and intervention phase II will be counted for monitoring adherence. The licensed acupuncturists with more than 5 years of experience with acupuncture will be trained for a standard intervention procedure before this study. Patients will be given paracetamol sustained-release tablets (Tylenol; Shanghai Johnson Pharmaceutical Co., Ltd.) as a rescue medication when they have excessive pain, and the administration of rescue medication will be recorded in detail.

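### Randomised patients are removed from the study for unpermitted treatment or missed sessions, so LOCF replaces obtainable outcomes in the main ITT analysis

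*Protocol article*

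**What the plan says.** The second part of the Exclusion criteria section of the protocol article applies after randomisation: "During the trial period, patients with KOA who meet the following criteria will be excluded from the study". It has four triggers:

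1. "protocol violation such as taking analgesic without permission", or receiving other treatment that could interfere with the acupuncture effect;
2. withdrawal of consent;
3. "missing more than 6 of 24 acupuncture treatment sessions", counted over both phases together;
4. "occurrence of a serious adverse event that the doctors consider should lead to termination of trial participation".

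Under Clinical data analysis, ITT is the main analysis: "ITT analysis will be performed to analyze all randomized data". Missing values are filled by LOCF. The per-protocol set requires at least 10 sessions in each phase and all four fMRI scans. The Interventions section gives 12 sessions per phase, allows paracetamol as rescue, and says that "the number of treatments received by each patient at intervention phase I and intervention phase II will be counted for monitoring adherence". Nothing in the article says that outcome assessment continues after exclusion.

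**The concern.** The list puts non-adherence and outside treatment beside consent withdrawal and a serious adverse event that ends trial participation. The natural reading is that exclusion stops the patient's participation, and with it the later NRS, WOMAC and SF-MPQ assessments. If the trigger falls in phase I, the whole second phase is lost. LOCF then supplies those values in the analysis meant to include everyone. If exclusion instead means removal from the analysis, it contradicts the ITT statement.

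The specific effect is each patient's acupuncture change minus sham change, and the crossover was chosen to allow that contrast. Losing part of a phase loses that patient's contrast. Unpermitted analgesic use can plausibly depend on pain, the primary outcome, so the missing values may be informative. The nonspecific effect is the change during the sham phase, so carrying a phase baseline forward sets it to zero for that patient.

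Consent withdrawal is not disputed. Permitted paracetamol narrows trigger 1 to analgesics taken without permission and other interfering treatment.

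**Working it through.** **Attendance rule against the per-protocol set (document figures only).** Let m1 and m2 be the sessions missed in each phase, each from 0 to 12, giving 13 × 13 = 169 patterns.

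- Trigger 3 applies when m1 + m2 ≥ 7: 141 patterns. The other 28 stay in the study.
- The per-protocol session rule needs m1 ≤ 2 and m2 ≤ 2: 3 × 3 = 9 patterns, with at most 4 sessions missed in total.
- Overlap: 0. If m1 + m2 ≥ 7, one phase has at least 4 missed, so at most 12 − 4 = 8 attended.
- Patterns that stay in the study but fail per-protocol: 28 − 9 = 19, for example 3 + 3 or 6 + 0 missed.

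These are counts of patterns, not probabilities. Of the two clinical analysis sets, trigger 3 can affect only ITT.

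**When trigger 3 acts.** A phase I trigger needs 7 of that phase's 12 sessions missed. Assume each session is missed independently with probability p:

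| p | P(7+ of 24) | P(7+ of 12) | Share triggered in phase I |
|---|---|---|---|
| 0.05 | 0.01% | under 0.001% | 0.4% |
| 0.10 | 0.7% | 0.005% | 0.7% |
| 0.15 | 5.7% | 0.07% | 1.2% |
| 0.20 | 18.9% | 0.39% | 2% |
| 0.30 | 61.1% | 3.86% | 6% |

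Trigger 3 therefore acts almost entirely in phase II. Trigger 1 can act at any time.

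**Effect of LOCF on the specific effect (illustration).** None of these inputs is in the article:

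- a and s are the mean improvements on acupuncture and sham, and D = a − s. Removed patients are taken to have the same true effects as the rest.
- f is the fraction of the 60 removed under triggers 1 and 3: 5%, 10% or 20%, that is 3, 6 or 12 patients. The 20% attrition under Sample size is an all-cause planning allowance and does not cap f.
- k is the share of a phase's improvement already recorded at the last NRS before removal. It is 0 if there is no interim NRS; the schedule figure is not available.
- Values are carried across the washout, so an unobserved phase shows zero change.

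Removal in phase I, balanced between groups: acupuncture-first patients contribute k·a and sham-first patients −k·s, mean k·D/2. The estimate is (1 − f)·D + f·k·D/2 = D·[1 − f(1 − k/2)].

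Removal in phase II, balanced: contributions are a − k·s and k·a − s, mean (1 + k)·D/2. The estimate is D·[1 − f(1 − k)/2].

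| Share of D retained | f = 5% | f = 10% | f = 20% |
|---|---|---|---|
| Phase I, k = 0 | 95% | 90% | 80% |
| Phase I, k = 0.5 | 96.25% | 92.5% | 85% |
| Phase II, k = 0 | 97.5% | 95% | 90% |
| Phase II, k = 0.5 | 98.75% | 97.5% | 95% |

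If D = 1 NRS point, the shift runs from 0.0125 to 0.20. For an assumed SD of 2 to 3 for the within-patient difference and n = 60, the standard error is 2/√60 = 0.26 to 3/√60 = 0.39. If D = 0, balanced removal gives no bias.

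Removal in phase II from one group only, k = 0: the estimate is D + f·s if all removals fall in the sham phase, or D − f·a if all fall in the acupuncture phase. The article's responder threshold, "at least 2-point reduction on the NRS", is used here only as a scale. With a 2-point mean improvement in the affected phase, the shift is 0.05 × 2 = 0.1, 0.10 × 2 = 0.2 or 0.20 × 2 = 0.4 points, upward or downward.

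**Nonspecific effect.** If a fraction f of all patients have the sham change set to zero, the estimate is (1 − f)·s. For s = 2 this is 1.9, 1.8 or 1.6 points. Balance between groups does not cancel this.

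**The case against.** The strongest reply is that this is a condensed discontinuation list in a journal article. The full protocol may say that discontinued patients still attend a final assessment, and the flow, schedule and analysis figures are not available. That is possible, but the article states a rule: it says such patients leave the study, and no sentence limits this to stopping treatment.

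On size, much of the objection stands. Every f, k and effect is assumed, and balanced removal gives a shift below one standard error. If 2 to 3 is the SD within each period rather than of the difference, and the two periods are taken as uncorrelated, the standard error is √2 times larger (0.37 to 0.55). The one-sided case at f = 20% is extreme: 12 of 30 patients (40%) in one sequence and none in the other. Patient and evaluator blinding and the paracetamol rescue make that less likely. At ordinary attendance trigger 3 would remove few patients, and almost never in phase I.

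It is also fair that the article never says trigger 3 is meant to protect the per-protocol set. Its redundancy is not itself an error; it shows that dropping the trigger costs that set nothing.

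Last, using outcomes after outside analgesia estimates a treatment-policy effect, and analgesia in the sham phase would shrink the specific effect and inflate the nonspecific one. This is a real cost. But the plan has already chosen ITT on all randomised patients as its main analysis, and the per-protocol analysis is the place for the other question.

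**Conclusion.** The concern holds and should be fixed. On the plain reading, the rule ends data collection for patients whose outcomes could still be obtained, and LOCF replaces those outcomes in the main analysis. That attendance exclusion removes nobody from the per-protocol set is exact and rests only on the article's own session counts. Trigger 1 differs: the per-protocol definition has no matching rule, so that exclusion could affect both clinical sets.

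The size and direction of the bias cannot be determined from the article. Under the stated assumptions it is probably small next to sampling error when removal is balanced. It could be larger, in either direction, when removal is concentrated in one group. Confidence is medium, because the conclusion depends on exclusion ending assessment and the full protocol is not available.

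**What to change.** Reword the during-trial list so that unpermitted or interfering treatment (trigger 1) and missed sessions (trigger 3) are recorded as protocol deviations. For consistency, let a serious adverse event (trigger 4) end study treatment, with only withdrawal of consent to follow-up ending data collection. Keep the scheduled NRS, WOMAC and SF-MPQ visits in both phases for these patients, and use all observed data in ITT.

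Apply adherence and unpermitted treatment only in the per-protocol definition. The rule of 10 sessions per phase already covers attendance, and sessions are already counted by phase. A criterion for unpermitted analgesic or interfering treatment needs to be added.

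The cost is a protocol amendment during recruitment, and outcome visits that are already scheduled. Some non-adherent patients will still not attend, so part of the missing data will remain. The ITT estimate will then include outcomes after non-adherence or other treatment, and the report should say so.
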